**SYNOPSIS**

| **Title** | Measuring the impact of the French version of the Whiplash Book on both treatment approach and fears and beliefs among emergency physicians. A randomized controlled trial. |
| --- | --- |
| **Primary Investigator** | [name] |
| **Investigation Center** | CHU Clermont-Ferrand |
| **Objectives** | **Primary objective**  To determine what fears and beliefs physicians have about the consequences of whiplash. To measure the impact of a validated information booklet on emergency physicians' approach to management following a whiplash injury. |
| **Expérimental plan** | Randomized controlled study |
| **Physician number** | To assess the booklet's impact on whiplash beliefs measured by means of Whiplash belief questionnaire (WBQ), the sample size estimation was based on comparing the two study arms, with a two-sided Type-I error of 5% and statistical power of 90%. 22 subjects would be needed per randomization group in order to highlight an effect-size equaling 1 (which corresponds to a minimal difference of about 5 points for a standard-deviation between 4.78 and 5.37 concerning WBQ) under the previously described assumptions. It was eventually planned to include 24 subjects per randomization group in order to take into account any physician lost to follow up. |
| **Physician follow up** | Between 48 hours and one month |
| **Study Duration** | 4 months |
| **Study flow** | - V0 inclusion - Intervention (information leaflet) - Follow-up at least 48 hours |
| **Inclusion and non inclusion criteria** | The study was conducted involving a sample of 95 emergency physicians working in different hospital facilities in the Auvergne region, France. Hospitals were split into two groups: the six hospitals with the highest volumes, and the other seven hospitals, considered as local hospitals. |
| **Outcomes** | **Primary outcome** :  The primary endpoint was an assessment of fears and beliefs in the sample of physicians tested using a questionnaire, the WBQ, as previously validated in low back pain.  **Secondary outcomes** :  Secondarily, the physicians' fears and beliefs were also assessed using a second questionnaire initially validated in non-specific back pain and adapted to neck conditions. The FABQ (Fear Avoidance Belief questionnaire) in its validated French version comprises two independent scales: the physical activity FABQ and work FABQ. Approach to overall management in the emergency department meant the prescriptions and advice delivered to patients who suffer from whiplash injury. It was a secondary endpoint, evaluated in the form of a clinical case. |

Key words: Whiplash injury; Pamphlet; Beliefs; Education; Fear-avoidance.

.

**1- GENERAL INFORMATIONS**

**RESEARCH TITLE**: Measuring the impact of the French version of the Whiplash Book on both treatment approach and fears and beliefs among emergency physicians. A randomized controlled trial.

**DATA ANALYSIS**

Department of Physical Medicine and Rehabilitation, Clermont-Ferrand University Hospital, in collaboration with DRCI (Innovation and Clinical Research).

**STUDY PLANNING**

Submission to technical committee May 2015

Submission to ethical committee May 2015

Inclusion time: 3 months (September 2015 to November 2015)

Participation duration for each patient: 1 hour (inclusion visit) + 1 hour (follow-up questionnaires)

End of the study: December 2015

Data analysis and final report: February 2016

# 2- STUDY RATIONNALE

## 2.1 Background

Whiplash is defined as minor indirect trauma to the cervical spine following a collision from behind at low speed or when stopped. It is an acceleration-deceleration mechanism of energy transfer to the neck that occurs while driving in a town or city . The main obstacle to managing whiplash is that it is first and foremost a lesion mechanism and not a unique pathologic entity. This transfer of energy leads to bone or soft tissue lesions that can result in a variety of clinical manifestations.

Whiplash trauma and the resulting whiplash associated disorders have been the subject of much attention in the scientific literature and remain a major public health problem .

The most commonly encountered symptoms are neck pain, headache, low back pain, shoulder pain, as well as visual impairment . Patients can be categorized by lesion grade according to the Quebec task force classification . Following a whiplash injury, 44% of patients are asymptomatic at 1 month following the trauma, 65% at 12 months, and 75% at 5 years . However, it is not unusual for neck pain to become chronic, and when this occurs, there may be serious consequences on a social, professional and financial level.

Of the demographic and accidentological factors most often associated with chronic neck pain, there are the following parameters: initial pain intensity, a high number of initial symptoms, anxiety, and severity of the injury as perceived by the patient . Even though the role of the initial episode should not be ignored, progression to chronic pain is probably multifactorial and, like non-specific low back pain, psycho-social factors, and in particular patient fears and beliefs , seem to play an relevant role, as do environmental factors.

2.2 Practice guidelines

Management following whiplash injury can make use of the recommendations as published in the literature . The decision to conduct radiographic assessment should be guided by validated clinical criteria as defined by the Canadian C-Spine Rule . This involves a quick return to normal personal and work activity with the help of effective pain relief, in addition to the performance of specific mobilization exercises. This information can be found in the French National Authority For Health (HAS) guidelines which state that "active mobilization techniques provide short-term benefit if implemented early ." Most of these points were also stated by the South Australian Centre for Trauma and Injury Recovery in 2008 . Healthcare professionals must reassure and educate their patients that post-traumatic pain is normal, and that they need to remain active and maintain physical activity in order to improve their prognosis.

The professional consensus is that it is useful to provide targeted information at an early stage in whiplash settings in order to reduce mistaken fears and beliefs, as has been substantially demonstrated in non-specific low back pain.

As with back pain ,, healthcare professionals' fears and beliefs may influence their approach to management. Whereas most practitioners adhere to the approach of encouraging an early return to activity rather than excessive rest, patients do not follow these recommendations to any great extent . Less than 10% of healthcare providers correctly identify initial neck pain intensity and disability as the two main predictive factors of poor recovery . These mistaken beliefs are about the cause and progression of symptoms, and they provoke confusion in patients' minds It is vital to educate care-givers about the relevance of patients' fears regarding the prognosis of the initial trauma lesion, particularly when its pathophysiology is still unknown .

2.3 Interest to use a standardized booklet

A preliminary study enabled us to validate a French version of an information booklet that draws on validated data from evidence-based medicine. The booklet was "*Le guide du coup de fouet cervical*," the French version of The Whiplash Book . This study showed that fears and beliefs were considerably high in a population without neck problems who were working in hospitals. It also revealed that simply providing information could help lessen them.

**3- STUDY OBJECTIVE**

Our study's main aim was to determine what fears and beliefs physicians have about the consequences of whiplash. The secondary aim was to measure the impact of a validated information booklet on emergency physicians' approach to management following a whiplash injury.

**4- EXPERIMENTAL PLAN**

This was a prospective randomized controlled study conducted involving a sample of emergency medicine doctors.

4.1 Intervention

The intervention group was given the French version of "The Whiplash Book," an information booklet that has been validated in both English and French . This is a specific document that makes use of validated data from evidence-based medicine and that recommends returning to activity early and mobilizing the neck following whiplash injury. It aims to reassure patients and emphasizes the importance of mobilizing the neck early and of remaining active for better recovery. It provides illustrated guidance on the exercises to be performed. No particular intervention was conducted in the control group apart from giving them the two questionnaires.

4.2 Randomized controlled study

4.2.1 Experimental plan and justification

We will implement a multicenter randomized controlled trial comparing:

1) Single educational support in the form of an information booklet.

2) No particular intervention was conducted in the control group apart from giving the questionnaires.

The randomized controlled trial is the gold standard for therapeutic evaluation. Physicians randomized to the control group will not have specific information.

Physician will be blinded about the hypothesis. They will be informed that the objective of this study will be to evaluate an information booklet. However, the content of each take charge and the hypothesis of the study they will not be detailed. This strategy should limit bias, particularly the risk of bias assessment. This method is ethically acceptable because physician will be informed that for scientific reasons we cannot explain all the hypotheses of the study. Physician will all be informed at the end of the study hypotheses and results of the study if they wish.

4.2.2 Subjects selection

## 4.2.3 Outcomes

a)- Main outcome

The primary endpoint was an assessment of fears and beliefs in the sample of physicians tested using a questionnaire, the WBQ (Whiplash belief questionnaire) , as previously validated in low back pain. The French WBQ version has already been used to validate the Whiplash Book and later the French version of the same booklet. The WBQ assesses fears and beliefs about the consequences of whiplash, comprising nine items.

b)- Secondary outcomes

Secondarily, the physicians' fears and beliefs were also assessed using a second questionnaire initially validated in non-specific back pain and adapted to neck conditions . The FABQ (Fear Avoidance Belief questionnaire) in its validated French version comprises two independent scales: the physical activity FABQ and work FABQ. The physical FABQ measures fears and beliefs relating to physical activity in general, namely the actions of daily life. It comprises four items with the score varying from 0 to 24. The work FABQ measures fears and beliefs in relation to work activities. It comprises seven items with the score varying from 0 to 42. The term "back pain" was replaced by "neck pain".

Approach to overall management in the emergency department meant the prescriptions and advice delivered to patients who suffer from whiplash injury. It was a secondary endpoint, evaluated in the form of a clinical case.

## 4.3 Design of trial to be conducted

4.3.1 For the physician

***Inclusion visit***

Screening and inclusion will be made by the physician in charge of the study.

The following data will be collected in the case report:

- Demographic data (age, gender,)

- Socio-professional data (place of practice, length and time of practice, medical training or reading)

-Personal or family history of neck pain or Whiplash

- Fear and beliefs questionnaires: WBQ, FABQ.

***Assessments****:*

Once each of the department heads and the different physicians concerned had given their agreement to take part in the study, an initial questionnaire folder (containing the WBQ and FABQ) was sent by email and by post to each of the physicians drawn by randomization. Upon inclusion, demographic data was collected from the physicians (gender, age, place of practice, and length of time in practice), as well as any personal or family history of neck pain or whiplash. The physicians were also asked how often they encountered cases of whiplash.

Information about knowledge of whiplash injury was also sought. This included continuing medical training or recent reading (within the previous 3 years), and in particular knowledge of the different severity grades established by the Quebec Task Force classification , the radiologic recommendations of the Canadian C-Spine Rule , and lastly the latest HAS recommendation on physical therapy in post-whiplash neck pain .

Once the first questionnaire folder had been completed, a second folder was then sent to all physicians participating in the study. The intervention group was instructed to complete the questionnaires at least 48 hours after the intervention, that is, after reading the information booklet. The same items were included as in the initial folder, with an additional questionnaire enabling the intervention group to qualitatively assess the information booklet. If there was no response, reminders were sent by email, then by telephone, and lastly by post.

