# 5- STATISTICS

5.1 Subjects number

To assess the booklet's impact on whiplash beliefs measured by means of WBQ, the sample size estimation was based on comparing the two study arms, with a two-sided Type-I error of 5% and statistical power of 90%. Based on work proposed by [name] *et al.*  and an effect-size defined according to Cohen’s recommendations , 22 subjects would be needed per randomization group in order to highlight an effect-size equaling 1 (which corresponds to a minimal difference of about 5 points for a standard-deviation between 4.78 and 5.37 concerning WBQ) under the previously described assumptions. It was eventually planned to include 24 subjects per randomization group in order to take into account any physician lost to follow up.

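### Only the booklet arm receives a booklet appraisal form with the repeated WBQ and FABQ, and no order of completion or closed-booklet instruction is set, so the primary outcome is collected under avoidably different conditions in the two arms

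*Protocol*

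**What the plan says.** Under Assessments in Protocol section 4.3.1, the initial folder holds the WBQ and FABQ and "was sent by email and by post to each of the physicians drawn by randomization". Once it is completed, a second folder goes to all participants with the same items, "with an additional questionnaire enabling the intervention group to qualitatively assess the information booklet". The booklet arm is told to complete the questionnaires no sooner than 48 hours after reading. Non-responders are reminded by email, telephone and post.

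The primary endpoint is the WBQ (section 4.2.3): "The WBQ assesses fears and beliefs about the consequences of whiplash, comprising nine items". Of the booklet, section 4.1 says: "It aims to reassure patients and emphasizes the importance of mobilizing the neck early and of remaining active for better recovery". The booklet is given to the intervention group, and its return is not mentioned. Controls receive only the questionnaires.

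Section 4.2.1 relies on keeping physicians unaware of the hypothesis to limit bias, while telling them that an information booklet is being evaluated. Section 4.3.2, on bias reduction, covers randomization only.

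**The concern.** The WBQ is self-reported, and the booklet speaks directly to the beliefs it asks about. A form inviting the physician to judge the booklet, enclosed with the WBQ, can bring the booklet's messages to mind, or bring the booklet itself back to the desk, while the outcome is being answered. Only one arm receives that form.

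Any resulting shift would most plausibly move booklet-arm answers towards the booklet's message and so widen the difference from controls. Once the data are in, it could not be told apart from a real change in belief. The contents of the folder and the instructions for completing it are trial conduct fixed in the protocol, so a statistical analysis plan could not repair this later.

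**Working it through.** **1. The plan's own figure.** Section 5.1 sets a two-sided α of 0.05 and 90% power. The stated requirement reads: "22 subjects would be needed per randomization group in order to highlight an effect-size equaling 1". On the raw scale the target is described this way: "minimal difference of about 5 points for a standard-deviation between 4.78 and 5.37 concerning WBQ".

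- n per group = 2 × (z₀.₉₇₅ + z₀.₉₀)² / d² = 2 × (1.960 + 1.282)² / 1² = 21.01, rounded up to 22. The stated figure reproduces.
- Exact noncentral t power at 22 per group is 0.8997, or about 90%.
- With a 5-point difference, n is 20 at SD 4.78 and 25 at SD 5.37.
- The planned "24 subjects per randomization group in order to take into account any physician lost to follow up" allows for 2/24 = 8.3% loss: 22 / (1 − 2/24) = 24.

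These calculations treat physicians as independent, as the plan's own calculation does. The point made here does not change the sample size.

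**2. Conditions at follow-up, arm by arm (sections 4.1, 4.2.1 and 4.3.1).**

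| | Booklet arm | Control arm |
|---|---|---|
| Repeated WBQ and FABQ | yes | yes |
| Booklet appraisal in the same folder | yes | no |
| Order of forms fixed | no | not applicable |
| Instruction not to consult the booklet | none | not applicable |
| Told that a booklet is being evaluated | yes | yes |
| 48-hour instruction | yes | not stated |

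The second and fourth rows are the avoidable differences. The fifth is common to both arms, so the form does not reveal anything wholly new about the study.

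**3. Why baseline adjustment does not help.** Section 5.2 plans an ANCOVA on baseline score. Write the follow-up score as Y₁ = a + b·Y₀ + τ·G + e, with G = 1 for the booklet arm. If the conditions of measurement shift the recorded booklet-arm score by δ points, the recorded model is Y₁ = a + b·Y₀ + (τ + δ)·G + e. The coefficient of G then estimates τ + δ. Because δ arises after Y₀ is recorded and only where G = 1, adjusting for Y₀ leaves it untouched.

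**4. What a shift would do, if there were one.** The documents give no value for δ, so the values below are assumptions. Take SD 5, 22 per group, independent physicians, no true effect and a two-sided 5% t-test. The rejection rate comes from the noncentral t distribution with 42 degrees of freedom and noncentrality (δ/5) × √(22/2).

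| Assumed δ (WBQ points) | Rejection rate |
|---|---|
| 0 | 5% |
| 0.5 | 6% |
| 1 | 10% |
| 1.5 | 16% |
| 2 | 25% |
| 2.5 | 37% |

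A shift of half a point is almost harmless, while one of 2 points would matter. Nothing in the protocol says where in this range, or below it, the true value lies.

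**The case against.** The order of the forms is not stated. If the physician meets and completes the WBQ and FABQ first, the appraisal cues little. Retaining the booklet's content is also largely the treatment effect: section 2.3 rests the trial on information lessening fears and beliefs, and section 6.2 expects better knowledge. Only the extra cue from the form, or consulting the text while answering, could count as bias. Booklet physicians already know they were given a booklet, all physicians know one is being evaluated, and the 48-hour minimum limits immediate carry-over. Copying, moreover, does not depend on the appraisal form, since anyone who kept the booklet could consult it anyway.

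All of this stands, and it limits both the wording and the likely size. A reader might infer that the follow-up score partly measures prompted recall, or that the physician must reopen the booklet, unsupervised, at the same sitting. The protocol supports neither. It describes remote delivery with reminders and mentions no supervised completion, but it does not say where the forms are filled in, in what order, or with the booklet to hand.

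The objection does not remove the arm-specific package or the missing safeguard. That copying is possible without the form is a reason to add an instruction as well as to move the form.

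**Conclusion.** The point holds in a limited form. The protocol collects a self-reported primary outcome with an extra, booklet-focused form in one arm. It sets no order of completion and gives no instruction against consulting the booklet. The outcome is therefore not protected against cueing or copying, and the primary ANCOVA cannot remove a shift from either source. This rests on the stated contents of the second folder and on the protocol's silence about sequence and consultation, not on any evidence that a shift occurs.

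The size cannot be estimated and may be negligible. A reader might try to express it as a share of the 5-point target by assuming how many of the nine items move and by how much. The protocol gives neither the item scoring nor any basis for such counts, so no share should be quoted. The rejection rates shown in the working are a sensitivity range under assumed shifts, not a forecast. The point merits a minor change because that change is specific and cheap.

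**What to change.** Take the appraisal out of the second folder. Send it to the booklet arm only once the physician's completed WBQ and FABQ have been received, and the clinical case as well. Section 4.2.3 lists the case as a secondary endpoint, but section 4.3.1 does not say in which folder it is administered, so the rule should apply wherever that is.

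Print the same line on the outcome forms in both arms: answer from your own current opinion, without consulting any document. Record both measures in section 4.3.2.

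The cost is one extra email or posting to the booklet arm, one sentence on the forms, and possibly fewer returned appraisals. The appraisal is not a listed endpoint, so no planned comparison is lost, and the sample size is unchanged. The change does not make the arms fully alike: the 48-hour instruction is still addressed to the booklet arm only, and controls still receive no comparator document. It removes the one difference in the outcome package that is easily avoided.

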## 4.3.2 Bias reduction measures

Randomization :

Randomization was performed by computer by drawing lots with random block sizes and was conducted by a statistician working independently of the study. Seven hospitals were drawn to make up the intervention group (reading the booklet), whereas the other hospitals made up the control group (no specific intervention).

# 5- STATISTICS

5.1 Subjects number

To assess the booklet's impact on whiplash beliefs measured by means of WBQ, the sample size estimation was based on comparing the two study arms, with a two-sided Type-I error of 5% and statistical power of 90%. Based on work proposed by [name] *et al.*  and an effect-size defined according to Cohen’s recommendations , 22 subjects would be needed per randomization group in order to highlight an effect-size equaling 1 (which corresponds to a minimal difference of about 5 points for a standard-deviation between 4.78 and 5.37 concerning WBQ) under the previously described assumptions. It was eventually planned to include 24 subjects per randomization group in order to take into account any physician lost to follow up.

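### The 90% power in section 5.1 comes from a formula for independently randomised physicians, although section 4.3.2 randomises 13 hospitals, so the figure is unsupported for this design

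*Protocol*

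**What the plan says.** Protocol section 5.1, repeated in the synopsis, sizes the trial on a comparison of the two arms "with a two-sided Type-I error of 5% and statistical power of 90" per cent. It concludes that "22 subjects would be needed per randomization group in order to highlight an effect-size equaling 1", which it equates with "a minimal difference of about 5 points for a standard-deviation between 4.78 and 5.37 concerning WBQ". The only allowance is for attrition: "It was eventually planned to include 24 subjects per randomization group in order to take into account any physician lost to follow up". It gives no intra-hospital correlation, number of hospitals, physicians per hospital or design effect.

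Section 4.3.2 describes the allocation: "Seven hospitals were drawn to make up the intervention group", with the remaining hospitals as control. The synopsis describes the hospitals as "the six hospitals with the highest volumes, and the other seven hospitals, considered as local hospitals", which makes 13. It also says: "The study was conducted involving a sample of 95 emergency physicians working in different hospital facilities in the Auvergne region, France". Section 6.1 keeps the target at 24 per group.

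Section 5.2 makes the primary analysis an ANCOVA on baseline scores and names no hospital term for it. Centre appears as a random effect only in the further multivariate models.

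**The concern.** When hospitals are randomised, colleagues in the same hospital carry partly the same information, and the evidence on the treatment effect is limited by the number of hospitals. A calculation that counts physicians as independent omits both. The 90% is the only justification given for the sample size and it is stated twice.

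Two things are at stake, depending on how the trial is analysed:

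- If the analysis respects the hospital as the randomised unit, power may be below the stated figure, and a null result would be read as stronger evidence against a 5-point difference than it is.
- If the primary ANCOVA is run as written, without hospital, the cost falls on the type I error and the risk is a false positive.

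**Working it through.** **Inputs from the protocol.** Two-sided 5%, power 90%, effect size 1, 22 per arm, raised to 24 (section 5.1). Seven hospitals drawn to the booklet, the rest control (section 4.3.2). 6 + 7 = 13 hospitals and 95 physicians (synopsis). The 7 v 6 split by arm is inferred from these two places: 13 − 7 = 6.

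**Assumptions, not in the protocol.** ICC 0 to 0.20; baseline-to-follow-up correlation ρ of 0.3 or 0.5; coefficient of variation (CV) of hospital size 0.5 where stated. The effect size is kept at 1 throughout.

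**1. Reproducing the plan's figure.** n per arm = 2 × (1.960 + 1.282)² / 1² = 21.01, rounded up to 22. The non-central t power for 22 v 22 on 42 df is 0.8997. The match is exact, so no allowance for clustering is hidden in the 22.

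**2. Same numbers, hospitals as the randomised unit.** Physicians per hospital: 22/7 = 3.14 and 22/6 = 3.67. The design effect in each arm is 1 + (m − 1) × ICC. The variance of the standardised difference is (DE₁ + DE₂)/22, and power is taken from the non-central t on 13 − 2 = 11 df (critical value 2.201).

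Example at ICC 0.10: DE₁ = 1 + 2.14 × 0.10 = 1.214; DE₂ = 1 + 2.67 × 0.10 = 1.267; variance = 2.481/22 = 0.1128; non-centrality = 1/√0.1128 = 2.978; power 77.4%.

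**3. Variants.** Baseline adjustment multiplies the variance by 1 − ρ² (0.75 at ρ = 0.5), taken to apply equally between and within hospitals. Unequal sizes replace m by m(1 + CV²). For 95 physicians, n per arm is 95/2 = 47.5.

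| Power (%), effect size 1, 11 df | ICC 0 | 0.05 | 0.10 | 0.20 |
|---|---|---|---|---|
| 22 per arm, unadjusted | 85.5 | 81.4 | 77.4 | 69.9 |
| as above, hospital-size CV 0.5 | 85.5 | 79.9 | 74.6 | 65.2 |
| 24 per arm, no losses, unadjusted | 88.3 | 84.1 | 79.8 | 71.9 |
| 22 per arm, ρ = 0.3 | 88.5 | 84.8 | 81.1 | 73.9 |
| 22 per arm, ρ = 0.5 | 93.6 | 90.8 | 87.8 | 81.7 |
| 24 per arm, ρ = 0.5 | 95.3 | 92.6 | 89.7 | 83.4 |
| 95 physicians, unadjusted | 99.3 | 97.1 | 93.3 | 83.7 |

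The drop to 85.5% at ICC 0 is due entirely to using 11 df. By the normal approximation alone, 22 per arm holds 90% up to an ICC of about 0.02.

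**4. If hospital is left out of the analysis.** The nominal critical value 1.96 behaves as 1.96/√DE, with DE averaged over the arms. With 22 per arm:

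- ICC 0.05: DE = 1.120, effective value 1.852, type I error 6.4%.
- ICC 0.10: DE = 1.240, effective value 1.760, type I error 7.8%.
- ICC 0.20: DE = 1.481, effective value 1.611, type I error 10.7%.

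Larger hospitals make this worse. With 95 physicians, m = 6.79 and 7.92, so at ICC 0.10 the average DE is (1.579 + 1.692)/2 = 1.635, the effective value 1.533 and the type I error 12.5%. For the ANCOVA, the relevant ICC is the one remaining after baseline adjustment.

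**The case against.** **The size of the loss rests on quantities that the protocol does not give.** This stands. ICC, size variation and baseline correlation are all assumed. A reader might infer that the trial simply does not have 90% power. The documents do not support that. The primary analysis in section 5.2 is baseline-adjusted, and at a correlation of 0.5 power with the planned 24 per arm is about 93%, 90% and 83% at ICC 0.05, 0.10 and 0.20. With 95 physicians it is about 97%, 93% and 84% even without adjustment. Equally, these figures do not rescue the stated 90%: section 5.1 uses neither the correlation nor the 95, and at a correlation of 0.3 with 22 per arm power stays below 90% at every ICC shown.

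**The harm may run the other way.** This stands too. A reader might take the only danger to be an over-read null result. The primary ANCOVA as written names no hospital term, so the first consequence of following the text literally is an inflated type I error. The power figures on 11 df describe an analysis that section 5.2 does not name as primary.

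**The unit of randomisation is not worded uniformly.** Sections 4.2.1 and 4.3.1 speak of physicians being randomised or drawn. Section 4.3.2 is the dedicated randomisation text and says that hospitals were drawn, so it is the better guide. The 7 v 6 split is an inference and should be stated outright.

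**The arithmetic itself is right, and much of the protocol is in the past tense.** Both are true. The fault is in what the formula assumes about the design, and correcting it would be partly descriptive. The primary model is a different matter, because changing it alters the reported inference.

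**Conclusion.** The point holds in this form: the 90% in section 5.1 and the synopsis belongs to a trial of independently randomised physicians and is not supported for one that allocates 13 hospitals. On the protocol's own 22 per arm, without adjustment and on 11 df, power is 85.5% at ICC 0 and about 81%, 77% and 70% at ICC 0.05, 0.10 and 0.20, with a further loss if hospital sizes differ. That is likely here, since the synopsis groups the hospitals by volume. Baseline adjustment or a larger analysed sample may offset some or all of this, so actual power is uncertain; it is not shown to be inadequate. The linked consequence is that a primary ANCOVA without hospital would have a type I error of about 6.4% to 10.7% over ICC 0.05 to 0.20 with 22 per arm.

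That 22 was calculated without clustering is certain. The size of the effect depends on the assumed ICC, size variation and baseline correlation, and on taking 11 df as the reference.

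**What to change.** In section 5.1 and the synopsis, replace 90% with a power range for the hospital-randomised design. State the 7 v 6 hospitals, the expected physicians per hospital and their variation, an ICC range with its reason, the baseline correlation assumed, and the number planned for analysis, reconciling 24 per group with the 95 in the synopsis.

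In section 5.2, include hospital as a random effect in the primary baseline-adjusted model, with a small-cluster degrees-of-freedom correction, so that the restated power and the primary test refer to the same analysis. Changing section 5.1 alone would describe the power of a test that is not the primary one.

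The cost is one recalculation, a rewritten paragraph and a changed model statement. The stated power becomes less favourable and the confidence interval somewhat wider. No extra recruitment is needed.
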